#### Behavioral activation tasks

Behavioral activation directly changes actual behavior and reinforces new behavior. This micro-intervention operationalizes the general change mechanism *targeting behaviors to realize practice.* In the present coaching intervention, participants receive three new suggestions of behavioral activation tasks every Sunday, which fit to their chosen change goal [25, 26]. Out of these three suggestions, participants select one behavioral activation task with the goal to implement the task in their daily routine during the following week. Examples for behavioral activation tasks are: “Don’t procrastinate and do things right away.” (Productiveness, Conscientiousness), “Tidy up a part of your flat every day.” (Organization, Conscientiousness) or “Take a photo of something beautiful every day.” (Aesthetic Sensitivity, Open-Mindedness). In total, we developed 12 behavioral activation tasks for each of the nine Big Five personality trait profiles (108 behavioral activation tasks in total) (cf. [59]).

#### Self-reflection

Self-reflection is a tool to exercise introspection, learn from experiences including successes and failures. This micro-intervention is included to target the general change mechanism *targeting thoughts and feelings to realize insight.* Different tools to exercise self-reflection are included in the weekly core themes, which change every week to enhance adherence and are embedded in every dialogue in the evening (Table 1).

#### Resource activation

Resource activation capitalizes on individual and interpersonal strengths and resources***.*** This micro-intervention is included to target the general change mechanism *activating strengths and resources to realize strengths-orientation*. Tools including resource activation are also included in the weekly core themes, which change every week (Table 1).

#### Individualized progress feedback

Individually tailored progress feedback is one of the most commonly used change techniques in smartphone-based health interventions [13] that helps people to focus on their discrepancy awareness. This micro-intervention targets the general change mechanism *actuating discrepancy awareness.* Participants constantly receive individualized graphical feedback on the dashboard of the PEACH app (Fig. 2). For instance, they can check whether they are already approaching their change goal compared to the beginning of the intervention. Additionally, they get feedback about how often they had opportunities to show their weekly implementation intention and how often they actually implemented it during the last seven days. Furthermore, they can check their momentary status (bronze, silver or gold status) and see the credits they have already earned during the intervention (Fig. 2).

### Assessment Strategy

The assessment strategy includes (1) a screening assessment (self-reported), (2) an outcome assessment (self-reported and observer-reported), (3) a process assessment (self-reported), and (4) smartphone sensing. An overview is shown in Table 2. These different types of assessments will be further elaborated in the following.

**Table 2 Tab2:** Measures

				Intervention				
	Screening	Pre-Test	Experience Sampling	Daily	Weekly	Post-Test	Follow-up	Evaluation
Screening								
Symptom-Check List (SCL-K11; [62])	x							
Depression Scale (ADS-K; [63])	x							
Demographics	x	x						
Main Outcome Assessment – Self report								
Big Five Personality Inventory (BFI-2; [59])		x				x	x	
Main Outcome Assessment – Observer Report								
Big Five Personality Inventory (BFI-2-S; [61])		x				x	x	
Process Assessment – Self report								
Big Five Personality Inventory 2 (BFI-2-S; [61])					x			
Big Five personality states			x	x				
Affect (PAM; [75])			x	x				
Information about current environment			x					
Stress level			x					
Realization of implementation intention				x				
Opportunities for realization of implementation intention				x				
Strength of change goal		x			x	x	x	
Subjective perception of change					x	x	x	
Learning experience					x			
Inclusion-of-the-Other-in-the-Self [71]		x			biweekly	x		
Working Alliance Inventory (WAI-SR, [67])		x			biweekly	x		
Perception of Robots [69]		x				x		
Trust [70]		x			four-weekly	x		
Further Outcome & Control variables – Observer report								
Demographics		x				x	x	
Type and closeness of relationship		x				x	x	
Time spent with target person		x				x	x	
Further Outcome & Control variables – Self report								
Willingness to change [60]		x						
Implicit theory of personality [64]		x				x	x	
Satisfaction with life domains [2]		x				x	x	
Satisfaction with Life Scale [65]		x				x	x	
Rosenberg Self-Esteem Scale (RSES; [66])		x				x	x	
Engagement in self reflection		x				x		
Engagement in practice		x				x		
Feedback on components of the coaching								x
Technology acceptance scales [74]		x						x
Internet users’ privacy concerns [89]		x						
Technical anxiety [90]		x						
Manipulation check items		x						x

#### Screening assessment

During the onboarding process (Fig. 1), participants will respond to two screening questionnaires to check for eligibility. Participants are directed from the PEACH app to the online survey tool (limesurvey.org), so that they can answer the screening questionnaires on their smartphone. Short forms of the Symptom-Check List (SCL-K11; [62]) and Depression Scale (ADS-K; [63]) will be used to assess mental health disorders and other psychosocial problems (Table 2). Individuals with scores above the cut-off value in the SCL-K11 (≥14) and above the cut-off value in the ADS-K (≥19) will be excluded and are provided with information and contact details of the psychological counseling service of the University of Zurich.

#### Outcome assessment

##### Self-reports

The self-reports include a pre-test, a post-test and a three-month follow-up assessment. Pre-test assessment will take place before the intervention, post-test assessment after the intervention and the follow-up assessment three months after the end of the intervention to check whether personality changes could be maintained over a longer period of time or revert over time. At all points of measurement participants will be automatically directed from the PEACH app to the online survey tool (limesurvey.org) to answer all questionnaires on the smartphone (Fig. 3). The main outcome assessment includes the Big Five Inventory 2 (BFI-2; [59]) to assess the Big Five personality traits and trait-related facets. Further outcome variables and control variables are willingness to change [60], implicit theory of personality [64], satisfaction with life (SWLS; [65]), satisfaction with life domains [2], and self-esteem (RSES; [66]) (Table 2).

**Fig. 3 Fig3:**
[figure not shown]
User interface for survey data collection. *Note.* Experience sampling assessment with self-reports (left) and daily diary assessment of the Big Five personality states (right) using bipolar adjective items (ad hoc translation from German)

Main outcomes regarding the relationship building process with the conversational agent include the following: Working alliance will be assessed using an adapted short-version [67] of the Working Alliance Inventory (WAI-SR) [52] based on Kiluk et al.’s [68] work, who adapted the complete WAI to measure working alliance with a technology-based intervention (WAI-Tech). To further understand the perception of the conversational agents, the Perception of Robots scale [69] and trust measures [70] to assess trust development mechanisms will be included. Interpersonal closeness will be measured with the Inclusion-of-the-Other-in-the-Self (IOS) scale [71], an established and reliable instrument to measure perceived closeness of a relationship [72]. Manipulation checks for perceived self-awareness of the conversational agents [73] will be conducted every four weeks to confirm that the manipulation had been scripted thoroughly throughout the 10-weeks of intervention.

Overall satisfaction with the app, ease of use, perceived enjoyment, and perceived usefulness will be measured after the first week and at the end of the intervention [74] to identify differences in the perception of the conversational agent due to differences in the usability of the app. Moreover, we are interested in qualitative feedback of users at the beginning of the interaction with the conversational agents (first impression) and at the end of the intervention to eventually improve the interaction with and perception of the conversational agents.

##### Observer reports

In addition to self-reports, observer-reports by close others will be assessed. At the beginning of the study, participants will be asked to share a link to the online observer-report questionnaires with at least three close friends, family members or their intimate partner. Observer-reports include the Big Five personality traits (BFI-2-S; [61]), type and closeness of the relationship and time spent with the target person. Observer-reports will be assessed at pre-test, post-test and follow-up assessment (Table 2).

#### Process assessment

##### Experience sampling with self-reports

One week before the intervention and one week after the intervention (Fig. 1), there will be an experience sampling with self-reports including four assessments per day (Fig. 3) at random times once in each of four predefined time windows: 9:30 a. m. - 11:30 a. m., 12:30 p. m. - 14:30 p. m., 15:30 p. m. - 17:30 p. m., 18:30 p. m. - 20:30 p. m. Participants will be asked to behave the first week as normal as possible and not to change anything in their behavior in order to measure their baseline behavioral signatures. After the intervention, participants are asked to answer the same experience sampling questions again during one week. This allows to check for changes in the behavioral signatures as a result of the intervention. Experience sampling assessments include the photographic affect meter (PAM; [75]) to assess momentary affect, five bipolar adjective items to assess the Big Five personality states (presentation in a random order), a few questions about the current location (e.g., indoors versus outdoors), activity, and social environment (e.g. alone versus with other people) at the moment, and a single item to measure momentary stress.

##### Daily diary and weekly self-report assessments

During the intervention, there will be daily diary and weekly measurements to assess individual change progress. The photographic affect meter (PAM; [75]) and ten bipolar adjective items to assess Big Five personality states will be used on a daily basis every evening. Additionally, participants are asked every evening whether they had opportunities to show their individual implementation intention and whether they could perform their implementation intention. There will be a weekly assessment every Sunday including a short version of the BFI-2 (BFI-2-S; [61]) (Table 2).

#### Smartphone sensing

Smartphone applications can get access to data from sensors and usage logs (e.g. location, surrounding devices via Bluetooth, logs of application usage and phone calls), which allow objective measurement of behavior, and inferences about users’ personality [76, 77]. Using this data, it may also be possible to detect changes in personality over short periods of time. If the application detects changes in behavior that are consistent with desired changes in personality and associated with the use of the PEACH app, this would constitute complementary evidence for PEACH’s effectiveness.

### Technological Background of the Intervention

The smartphone-based coaching intervention is based on the MobileCoach (www.mobile-coach.eu). The MobileCoach is an open source platform for the design, delivery and evaluation of scalable smartphone-based interventions [40, 43, 78]. It is available via the research and industry-friendly Apache 2 license and follows a client-server model. The rule-based intervention logic and messages are defined by intervention authors on the server. MobileCoach then acts as a conversational agent and uses these rules to send out the intervention messages to client applications on mobile devices. MobileCoach also allows to react to answers given by intervention participants and can deliver these interventions via the widely available short message service (e.g., to lower the threshold for participation and to maximize the reach of an intervention) and/or via dedicated mobile messaging apps for Apple’s iOS and Google’s Android platform. The mobile messaging apps allow not only to fully customize the user experience to a particular target group (e.g., the look and feel of the app with various conversational agents) but also to use sensor data from smartphones and/or other connected devices to deliver just in time adaptive interventions based on end users’ states of receptivity and vulnerability [79, 80].

Previous studies have demonstrated the effectiveness and reach of MobileCoach-based interventions with regard to problem drinking in adolescents [58] and perceived ease of use, enjoyment, therapy adherence and scalability in a childhood obesity intervention [40, 43]. In addition to delivering interventions, MobileCoach is also used for the collection of intensive longitudinal data in situ (e.g., for ecological momentary assessments), for example in a clinical trial on stress disorders.

In the PEACH study, the iOS and Android apps of MobileCoach are used to guide participants through the micro-interventions, providing motivation, promoting commitment, and reminding them to complete questionnaires. During these conversations, a combination of pre-defined answers and free-text input is used to constrain the dialog along pre-defined counselling paths and to give the participant autonomy where needed (e.g., for the definition of implementation intentions in the if-then form). With a swipe-to-the-right gesture or via a menu button, participants can open the sidebar of the PEACH app (Figure 2) from which they can navigate to (a) their personal dashboard, (b) a media library used for psychoeducation video clips which are unlocked along the intervention path, (c) a second chat channel “Support-Team” for a traditional WhatsApp like communication with the study team (e.g., to clarify technical questions and comments), or (d) to a page for frequently asked questions about the PEACH study and the PEACH app. From the sidebar, participants can also navigate back to the chat channel with the conversational agent and to the dashboard (Fig. 2). The dashboard gives an overview of the self-selected personality change goal and the weekly individual implementation intention. It also provides a traffic light, whether an individual was able to get closer to its intended personality change goal (green light), further away from it (red light) or whether there is no change in any direction (yellow light). For this comparison, participants self-reported ratings of the Big Five personality states (bipolar adjective scales) for the last seven days will be compared to his/her ratings of the Big Five personality states of the first week of the intervention. The traffic light changes to green or red when the averaged delta of scores between the last and the first week is more than half a standard deviation. The rationale of using a time window of seven days was to account for natural variance in daily ratings of study participants. The dashboard also visualizes whether and on which day participants had opportunities to pursue and in fact realize their individual implementation intention during the last seven days. Eventually, the personal dashboard illustrates their latest credit score and the remaining time of the intervention program.

### Data Analyses

Longitudinal multilevel modeling (MLM) and structural equation modeling (SEM) will be used to analyze the (intensive) longitudinal, nested data structure and change over time [81–84]. Both data-analytic methods are specifically suitable to model change explicitly as a function of time and can be used to formulate equivalent models, providing identical estimates for the collected data. Separate models will be analyzed including the outcome assessments at pre-, post- and follow-up (self-reports and observer-reports), daily diary assessments, and weekly self-report assessments. Predictor/control variables will be added to the models to examine how individual growth will be moderated by variables such as intervention condition, change goal or willingness to change. The statistical modeling programs Mplus [85], and updated R packages (R Core Team, Vienna Austria) will be used to estimate the growth curve models.

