### Participants and Recruitment

The targeted sample will include at least 900 German-speaking adults, who install the PEACH App on their smartphones, give informed consent, pass the screening, fill in the pre-test assessment and start with the intervention. To assure an adequate power to detect statistical significance and to demonstrate a small to medium effect of a pre-post time by group interaction we require data from 300 participants. Assuming an α error level of 0.05, a statistical power (1-β) of 0.80, and a correlation of 0.40 between the pre- and post-measurements and 75 completers for each group, we would be able to detect a small effect of Cohen’s *d* = .22. Computing power for repeated measures, which is the case in this study, is more complex. As such, this power analysis only gives a rough idea of the effect sizes the study could reasonably detect. In a similar study [33], 67% of participants completed the post-test survey after 6 weeks, from a cohort of 273 who started the intervention. Based on this estimate and taking the longer duration of this study into account, we expect even more attrition. Should drop-out rates be higher than expected, we may recruit additional participants to ensure sufficient statistical power. To be eligible for the study, participants must be: (1) 18 years or older; (2) able to read German; (3) not in a psychotherapeutic or psychiatric treatment; (4) owner of a smartphone (Android or iOS) with mobile internet connection; and (5) interested and motivated to participate at the intervention and to change some aspects of their personality. The focus of this intervention study is explicitly on healthy adults. Thus, adults with mental health disorders and other psychosocial problems will be excluded. Participants will complete an online eligibility screening that checks for the inclusion criteria. Excluded candidates with mental health disorders and psychosocial problems will be provided with an information and contact details of the psychological counseling service of the University of Zurich.

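### The pre/post/follow-up model leaves out the weekly and daily scores of the same traits, so within-person change is exposed to bias if dropout follows recorded progress

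*Protocol article*

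**What the plan says.** On method, Data Analyses says "Longitudinal multilevel modeling (MLM) and structural equation modeling (SEM) will be used to analyze the (intensive) longitudinal, nested data structure and change over time", and then "Separate models will be analyzed including the outcome assessments at pre-, post- and follow-up (self-reports and observer-reports), daily diary assessments, and weekly self-report assessments". It adds that predictors such as condition, change goal and willingness to change will enter the models. It names Mplus and R as software. It states no missing-data method.

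On outcomes, the Self-reports section says "The main outcome assessment includes the Big Five Inventory 2". Table 2 lists the full BFI-2 at pre-test, post-test and follow-up only. Between those points the same traits are measured in two other ways. One is a short form: "There will be a weekly assessment every Sunday including a short version of the BFI-2". The other is a set of bipolar state items answered each evening.

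On attrition, Participants and Recruitment reports that in a similar study "67% of participants completed the post-test survey after 6 weeks, from a cohort of 273 who started the intervention", and continues: "Based on this estimate and taking the longer duration of this study into account, we expect even more attrition". The same section gives the numbers: "The targeted sample will include at least 900 German-speaking adults", of whom "we require data from 300 participants".

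**The concern.** Likelihood estimation in a growth or structural equation model handles missing post-tests correctly when missingness depends only on what is in that model. In the outcome model as planned, the only information on someone who leaves in week 5 is the pre-test and the covariates. Five weekly scores and several weeks of daily ratings of the same trait exist for that person, but they sit in other models. If people leave because recorded progress is poor, the missing post-tests are not missing at random in the pre/post/follow-up model, although they would be if those scores were included.

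Such dropout is plausible. The Technological Background section describes a dashboard light that tells participants whether they are moving towards their goal, away from it, or not at all.

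Within-person change matters more here than in most randomised trials. The Design section gives the wait-list arms the same intervention after four weeks, and the Self-reports section places post-test after the intervention. On the text, every arm has been treated by post-test. The stated goal of showing effectiveness at post-test and three-month follow-up therefore rests largely on within-person change, which is the vulnerable quantity.

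**Working it through.** **1. Attrition range.** The cited study lost 1 − 0.67 = 33% at 6 weeks, and the article expects more. Recruiting 900 to obtain 300 leaves room for 1 − 300/900 = 66.7%. The article gives no expected rate, so 33%, 50% and 66.7% were used.

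**2. The article's own figure.** It states a detectable d of .22 with 4 × 75 completers, alpha 0.05, power 0.80 and pre-post correlation 0.40. For a time-by-group interaction with 4 groups and 2 occasions, the noncentrality is λ = f²·N·m/(1 − ρ), with N = 300, m = 2 and ρ = 0.40.
- At f = .1051, λ = .01105 × 600/0.6 = 11.05 and power is 0.80, so d = 2f = .21.
- At f = .11, λ = 12.1 and power is .838; d = 2f = .22.

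The stated .22 looks like f rounded to .11 before doubling. That has no bearing on this point. The value .22 is an interaction effect; it is used below only as a convenient size of true change.

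**3. Simulation inputs.** From the article: pre-post correlation 0.40, 10 weekly scores, the attrition range above. Assumed: linear change; reliability 0.8 (BFI-2) and 0.7 (weekly score); monotone dropout; weekly log-odds of dropout rising by 0, 0.25, 0.5 or 1.0 for each SD less progress on the latest weekly score. These inputs imply a true-score correlation of 0.40/0.80 = 0.50 and a variance of true change of 2 × 0.8 × (1 − 0.5) = 0.8, so an SD of √0.8 = 0.89.

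**4. Estimators.**
- Separate model: regress post on pre among completers, predict at the mean pre-test of everyone, subtract that mean. This is the maximum-likelihood estimate from pre and post alone.
- Joint model: regress each score on all earlier scores among those still observed, carry the means forward through the 10 weekly scores to post-test, subtract the mean pre-test.

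**5. Results, true change 0.22 SD.**

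| Log-odds per SD less progress | Separate, 33% loss | Separate, 50% loss | Separate, 66.7% loss | Joint, all loss rates |
|---|---|---|---|---|
| 0 | 0.22 | 0.22 | 0.22 | 0.22 |
| 0.25 | 0.26 | 0.28 | 0.32 | 0.22 |
| 0.5 | 0.30 | 0.35 | 0.41 | 0.22 |
| 1.0 | 0.36 | 0.45 | 0.57 | 0.22 |

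The bias is +0.04 to +0.14 SD at 33% loss and +0.10 to +0.35 SD at 66.7% loss.

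**6. Sensitivity to the assumptions.**
- Less variable change: with true change 0.30, SD of change 0.3 to 0.5 and about half completing, the separate model returns 0.33 to 0.49, a bias of +0.03 to +0.19.
- Opposite direction: with true change 0.30 and a log-hazard that rises by 0.5 per SD of progress (people leave on reaching their goal), the separate model returns 0.13 to 0.27.
- Dropout driven by the daily states: with true change 0.22, 50% loss and log-odds 0.5, the separate model gives 0.31, adding the weekly scores gives 0.27, and adding the daily states as well gives 0.22. The weekly scores alone remove 0.04 of 0.09.
- Dropout driven by unrecorded progress: in one set of assumptions the weekly scores remove only 24% to 40% of the bias.

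**7. Contrasts between arms.** With true changes of 0.22 and 0 and one common dropout rule (log-odds 0.5 and 1.0), the separate model estimates the difference of 0.22 at 0.20 to 0.22 (33% loss) and 0.18 to 0.21 (66.7% loss), slightly low. If two agents had the same true change and the same rule (log-odds 0.5) but lost 33% and 50%, they would show 0.295 and 0.346, a spurious gap of 0.05 in favour of the agent that loses more people.

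**The case against.** The strongest reply is that the article lists which data sets get their own model and says nothing about missing data. Separate outcome models do not rule out weekly scores as auxiliary variables in Mplus, and a journal article commonly leaves missing-data handling to the full plan. That stands as far as it goes: nothing in the text forbids the remedy. But the separation itself is stated, and a model run as described would not use those scores.

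Four stronger readings are tempting, and the documents do not support them.
- A reader might infer that the weekly data of dropouts are thrown away. They are not: the same sentence plans a weekly model, and a likelihood-based growth model would use them there.
- A reader might infer that the randomised comparison is badly biased. Arms with a common dropout rule move little, and the untreated wait-list contrast lies largely in the weekly data, which are modelled.
- A reader might infer that the agent comparison is biased. That requires retention to differ by agent. The Research Goals and Hypotheses section expects the self-aware agent to improve adherence, so the risk is real, but no differential loss is given.
- A reader might infer that weekly scores alone would cure the problem. The dashboard light uses the daily state ratings, so if the light drives dropout, the weekly scores remove only part of the bias.

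The size and even the direction of the bias rest on assumptions outside the article. Follow-up was not simulated.

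**Conclusion.** The point holds in a limited form. As planned, the outcome model ignores collected scores of the same traits in a trial that expects more than a third to leave, and its within-person pre-post change is unprotected against dropout that follows recorded progress. If those not progressing leave, a true change of 0.22 SD would be reported as about 0.26 to 0.36 at 33% loss and 0.32 to 0.57 at 66.7% loss. These figures assume the stated dropout strengths and reliabilities and the variable change implied by a correlation of 0.40; less variable change gives smaller bias. The bias reverses if people leave on reaching their goal and vanishes if dropout is unrelated to progress. It should not be set against the article's .22, which is a time-by-group effect. This is a cheap improvement to the plan, not an error that invalidates it.

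**What to change.** Estimate post-test and follow-up change in a model that also contains the weekly BFI-2-S and the daily state scores of the same trait. Three routes would serve: auxiliary variables under full-information maximum likelihood, a joint growth model, or multiple imputation that uses those scores. Keep the separate models as secondary analyses. Add a sensitivity analysis for dropout driven by progress that was not recorded, which no model of the recorded scores can fully correct. Expect less benefit at follow-up, because the weekly and daily scores stop with the intervention and say nothing about the three months after it.

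The change takes a sentence or two in Data Analyses. The data are already to be collected and Mplus is already named. The cost is more analysis work and a more complex model; many daily scores may need to be summarised, for example by week, for it to be estimable.
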